### Interventions

#### Intervention development approach

The Physical Activity at Work (PAW) intervention development was guided by the Social-Ecological Model, which highlights that behaviours are shaped by various factors on different levels [32, 33]. On the individual level, behaviours can be influenced by attitudes and motivations toward activity. Factors at the social level, such as support from colleagues to be physically active, and at the environmental level, such as conducive space to move can also have a significant influence. Finally, factors at the organisational level (e.g. structures and support in the form of employee encouragement) is likely to play an important role in this study context. Our intervention will address such key factors on each level. The intervention components include different Behaviour Change Techniques (BCTs) to encourage sustained behaviour change. BCTs are active ingredients of the intervention as they are supposed to motivate behavior change [34]. An additional file shows an overview of BCTs and SEM levels that are used in this study (see Additional file 2).

#### Information booklet

Both the control and intervention groups will receive an information booklet about the benefits of PA and “7 easy exercises to an active lifestyle” for the office environment. Creating awareness and educating the public on the health consequences of PA and SB is a common method used in health promotion policies. Thus, the information booklet will contain details on the negative consequences of SB and highlight the benefits of PA. In addition, the booklet containing easy exercises would lower the barrier by providing individuals with the knowledge to elicit personal change.

### Intervention group

#### Individual-level components

##### Fitbit

The intervention group will be given a Fitbit device (Inspire HR) to track their PA throughout the trial. The proper use of the device will be explained in a self-help program booklet. Fitbit is an activity device that uses a tri-axis accelerometer to provide real-time feedback and allows self-monitoring of steps, as well as calories burned, distance covered, active minutes, heart rate, time asleep each day and proportion of hourly activity completed amongst others [35]. It provides feedback through a smartphone app via Bluetooth connection. The device also sets haptic vibration feedback for hourly activity during office hours (9 am to 6 pm) to nudge participants to walk at least 250 steps each hour. Participants will be encouraged to wear the device as frequent as possible to obtain the most accurate results.

##### Lottery-based incentives

Members in the intervention group will be eligible for a weekly performance-based lottery as a form of financial incentive to be physically active. To be eligible, participants will need to complete at least 70% of the recommended number of short breaks (i.e. at least 14 breaks per week out of 20 breaks), with a minimum of 100 steps during each break. Each week, a winner will be randomly selected among eligible participants and will receive 500 THB (US$ 16). Such incentives have been shown to be effective in motivating health-related behaviour change [34]. Adherence to the movement breaks will be measured using the Fitbit devices. Fitbit intraday data will be downloaded, providing minute-by-minute data that will be available through a web application programming interface (API).

#### Physical environment-level components

##### Posters

The intervention group will also be exposed to posters of exercises and stretching, posters with information about the health consequences of SB and PA and posters with details about the PAW study. The posters will be displayed in participants’ offices to encourage them to be physically active. The posters are in an additional file (see Additional file 2).

#### Social-level components

##### Team movement breaks

The social intervention consists of organising short group-based movement breaks, with each cluster forming a team. Each cluster will be encouraged to take four movement breaks of at least 4 min each at 9.30 am, 10.30 am, 2.30 pm and 3.30 pm, within a 60 min time window after the listed timings. An exercise or dance video with music will be played, and participants are encouraged to dance/exercise along with the video. Alarms will signal that it is time for a movement break. If participants work from home, they will be encouraged to join the breaks together online through video conferencing software such as Zoom.

##### Team-based incentives

The weekly winner of the performance-based lottery will receive a bonus of 500 THB (US$ 16) if at least 70% of the teammates also met the recommended target (by completing at least 70% of the weekly recommended short breaks). This bonus is designed to further leverage peer effects by reinforcing accountability and peer support to the team [36, 37]. Participants will be informed about the financial incentives in advance in the information booklet provided to them at the start of the intervention.

#### Organisational-level components

##### Leadership support

Leaders within DMS will encourage participants to take part in the study via Line and Facebook, offering rewards and recognition to participants who win in a weekly lottery (see **lottery-based incentives** above for more details). Line™ is a freeware app for instant communications on electronic devices such as smartphones, tablet computers, and personal computers that is used by 44 million residents in Thailand or 63% of the Thai population [38]. Participants who meet the recommended short break targets will receive recognition for their efforts by email, and each weekly winner of the performance-based lottery will receive their prize from the head of the participating division.

### Outcomes and measurements

#### Data collection

The duration of the research will be 18-months from the start of the intervention (6-months of intervention and 12-months follow-up, in addition to the baseline data collection), and participants will be requested to remain continuously enrolled during this period. Figure 1 provides an overview of the timeline of the PAW trial. Survey data will be collected at four time points: baseline, 6th month, 12th month and the 18th month after baseline assessment. Data will be collected by a trained research team, supervised by the core research team to ensure the quality and consistency of the data collected. The survey will be interviewer-administered. Trained physicians or nurses will take invasive cardiometabolic measurements at baseline, 6th month, and 12th month. Demographic information will only be measured at baseline. The main challenge will be to trigger sustained adherence to short breaks and not just a short-term behaviour change. In that regard, implementing a follow-up period that is sufficiently long to assess these long-term effects is essential. As a token of appreciation, all participants who have completed follow-up at 6th, 12th and 18th month will receive compensation of 500 THB (US $16) at 6th month, and 250 THB (US$ 8) each at 12th and 18th month. In total, they will be compensated 1000 THB (US $32) if they have participated until the end of the trial.

**Fig. 1 Fig1:**
[figure not shown]
Study Overview

#### Primary outcomes

The primary outcome of this study is the change in sedentary time at 6th month follow-up. The accelerometer that will be used to measure SB is the ActiGraphTM wGT3X-BT tri-axial accelerometer (ActiGraph, Pensacola, Florida, USA). Participants will be advised to wear the ActiGraph accelerometer on their waist, above the right hip, with an elastic belt during their waking hours, excluding time spent in water-based activities, for a period of 10 days [39]. The device will be initialised at a sample rate of 60 Hz. Participants will be taught how to wear the device and will receive an information booklet with the instructions for reference. ActiGraph is a tri-axial accelerometer that measures SB and physical activities by categorising count data into different categories. These categories are defined as sedentary (150 and below counts per minute), light activity (151 to 2689 counts per minute), moderate activity (2690 to 6167 counts per minute) and vigorous activity (6168 and above counts per minute) [40]. Participants will be asked to wear the accelerometers during waking hours. Participants will be given activity logs to record the start and end date and time accelerometer wear. In addition, they will be asked to record their daily sleep and wake times as well as any activities, their frequency and duration, that they engaged in while not wearing the accelerometer (e.g. duration and frequency of water-based activities when they have to take off their accelerometer). The activity log will be used together with daily data to assess the adherence of wearing the ActiGraph accelerometers. To encourage adherence to wearing ActiGraph at night, participants will be given an additional 150 THB (US$ 5) per data collection. No incentive will be given if participants wear ActiGraph during sleep but not during the day. Participants will be able to receive an additional of 600 THB (US $20) in total if they participate in all data collection rounds, and wore ActiGraph both during the day and during sleep. Reminders to wear the accelerometers will be sent via the LINE messaging app.

#### Secondary outcomes

Secondary outcomes will include the impact of the intervention on PA such as time spent in light activities, and moderate to vigorous activities. The secondary PA outcomes will be measured using ActiGraph and the General Physical Activity Questionnaire (GPAQ) [41]. Other secondary outcomes include the change in on cardiometabolic outcomes. The cardiometabolic outcomes consist of the following physical measurements: waist circumference and neck circumference
systolic blood pressure and diastolic blood pressureresting heart ratebody weightheight and body mass index (BMI).

Weight and height will be measured without shoes to the nearest 100 g and 0.1 cm, respectively. Body mass index (BMI) will be calculated by dividing weight in kilograms with the square of height in meters. Systolic and diastolic blood pressures will be measured after the participants had rested for at least 5 min [42] with an automatic blood pressure monitoring by trained research assistants. Waist circumference (cm) will be measured at the middle point between the lowest rib and iliac crest in the standing position. Neck circumference (cm) will be measured with the head positioned in Frankfurt horizontal plane using non-stretchable plastic tape to the nearest 1 mm. It will be measured at the level just below the laryngeal prominence perpendicular to the long axis of the neck.

Blood collection and tests will be done by a certified, private laboratory team (NHEALTH) [43] which consists of nurses and laboratory technicians. 15 ml of blood will be collected in each data collection. HOMA-IR will be calculated by [Fasting insulin (mU/l) x fasting glucose (mmol/l)]/22.5. Participants will be required to fast for at least 10 h before the blood tests. We will also be collecting blood biomarkers outcomes:
fasting plasma glucose (HbA_1_c)fasting insulinhomeostasis model assessment of insulin resistance (HOMA-IR)serum uric acidlipid profilehigh sensitivity C-reactive protein (hs-CRP).

Study participants with abnormal biomarkers will be encouraged to see physicians using their own public health insurances under the UHC policy which cover non-communicable disease treatments for all Thai population.

#### Tertiary outcomes

Quality-Adjusted Life Years (QALYs) will be obtained from three surveys for cost-effective evaluation. One is the EuroQol-5 Dimension (EQ-5D-5L), where participants will be able to rate the severity of their disease [44]. The instrument encompasses five dimensions: mobility, self-care, usual activities, pain/discomfort and anxiety/depression. Participants will be asked to rate their health state on five levels of severity. QALYs will also be taken from work productivity, which will be assessed using the Work Productivity and Activity Impairment Questionnaire (WPAI) and musculoskeletal health which will be assessed using the Standardised Nordic Questionnaire [45]. In addition, the study will ask participants for demographic information and self-report of comorbidities. For candidates with pre-existing health conditions or metabolic risk factors (e.g. hypertension, diabetes, hyperlipidemia) we will collect additional data on the history of disease and medication dosage.

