#### Economic evaluation

The economic evaluation aims to report two pieces of cost-effectiveness information of the PAW program: 1) short-term economic impact; and 2) long-term economic impact. The analysis will be conducted from the perspective of public health care payer. The costing data will be collected from the trial. The longer-term costs, e.g. treatment costs for stroke and diabetes, will be retrieved from domestic literature or relevant cost databases [46].

First, we aim to conduct a person-level economic evaluation to report a short-term economic impact of the PAW program using the data from the trial within the study period. Based on data from the trial, we will compare the costs and outcomes of the intervention against the control using the net benefit regression framework [38]. Costs will include costs incurred to the MOPH, including intervention costs and costs of treating related health problems (e.g., musculoskeletal diseases, diabetes and hypertension). The effectiveness outcomes for this analysis will include: 1) absolute working hours; 2) absenteeism and presenteeism; 3) key clinical indicators, e.g. cardiovascular disease (CVD) risk scores; and 4) QALYs. Separate analyses will be conducted for each outcome. The output of this analysis will be expressed as an incremental net benefit of PAW compared to no PAW. We will also estimate incremental cost-effectiveness ratios (ICERs) over the study period, for example, the incremental cost of the PAW program (compared to no PAW) to obtain one more absolute working hour, and incremental cost for one more QALYs gained. The use of regression will allow us to adjust for potential confounders and to calculate the clustered standard errors using the sandwich variance estimators of Huber and White [39] to account for a clustered randomised design in which the outcomes of interest may be correlated. Uncertainty of the cost-effectiveness findings within the study timeframe will be characterised using a cost-effectiveness acceptability curve and a 95% confidence interval [40]. Moreover, additional subgroup analyses (e.g., by sex and age groups) could be explored.

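### The protocol names the WPAI and the Nordic questionnaire as sources of QALYs beside the EQ-5D-5L, but neither yields a utility; as written, the within-trial cost per QALY would not be valid

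*Protocol article*

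**What the plan says.** The Tertiary outcomes section opens with the source of the QALY: "Quality-Adjusted Life Years (QALYs) will be obtained from three surveys for cost-effective evaluation". It then goes through the three surveys.

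- The EQ-5D-5L: "One is the EuroQol-5 Dimension (EQ-5D-5L), where participants will be able to rate the severity of their disease". Its content is given as follows: "The instrument encompasses five dimensions: mobility, self-care, usual activities, pain/discomfort and anxiety/depression".
- The WPAI: "QALYs will also be taken from work productivity, which will be assessed using the Work Productivity and Activity Impairment Questionnaire (WPAI".
- The Nordic questionnaire, in the same sentence as the WPAI: "musculoskeletal health which will be assessed using the Standardised Nordic Questionnaire".

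The Economic evaluation section uses the QALY in a within-trial, person-level analysis. Its effectiveness outcomes begin with absolute working hours and continue: "2) absenteeism and presenteeism; 3) key clinical indicators, e.g. cardiovascular disease (CVD) risk scores; and 4) QALYs". It adds: "Separate analyses will be conducted for each outcome". One planned output is the "incremental cost for one more QALYs gained".

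**The concern.** A QALY is time weighted by a utility, that is, by a value placed on a health state. The WPAI records lost work time and impairment at work and in activities. The Nordic questionnaire records musculoskeletal symptoms. Neither attaches a value to a health state, and the article gives no conversion that would turn their answers into one.

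This is not detail left to an analysis plan. The article states where the QALY comes from, and two of the three sources cannot supply it.

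At stake is the within-trial cost per QALY. The last paragraph of the Background says that the cost-effectiveness analysis should allow comparison with the economic evaluations of other trials, and that the results should help shape the benefit package under Universal Healthcare Coverage. A QALY built partly on productivity or symptom answers would not support that comparison. With three named sources and no rule for choosing or combining them, more than one QALY could be computed, and the choice could be made after the data are seen.

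**Working it through.** No arithmetic applies: the article states no utility, QALY or ICER figure to reproduce. The check sets the sections side by side.

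**1. Is the three-source reading really in the text?** Yes. The opening sentence of Tertiary outcomes counts three surveys, and a later sentence makes productivity and musculoskeletal health further sources. Two separate statements agree, so this is not one misplaced word.

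**2. Can each source supply a utility?**

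| Survey | What it measures | Utility | Conversion stated |
|---|---|---|---|
| EQ-5D-5L | Health state on five dimensions | Yes, through an index | Not needed |
| WPAI | Work and activity impairment | No | None |
| Standardised Nordic Questionnaire | Musculoskeletal health | No | None |

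**3. Does the rest of the article agree?** It does not.

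- The Abstract (Methods/design) lists work productivity, musculoskeletal pain and quality of life as separate outcomes.
- Measurement timeline of outcomes lists the EQ-5D-5L, musculoskeletal health and the WPAI as separate tertiary outcomes. Table 1 gives each questionnaire its own row.
- Data analyses (Primary and secondary outcomes) names quality of life and productivity separately.
- Economic evaluation lists absenteeism and presenteeism apart from QALYs, with one analysis for each.

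Under Tertiary outcomes, work productivity would be a component of the QALY; under Economic evaluation it is an outcome beside the QALY.

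**4. Would anything be counted twice?** Only if WPAI or Nordic answers were merged with the EQ-5D-5L index into one QALY. The index already covers usual activities, which overlap with the WPAI, and pain/discomfort, which overlaps with the Nordic questionnaire. No section gives a rule for merging them.

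**5. Which results are exposed?** The within-trial QALY analysis, meaning its net benefit regression and its cost per QALY. The other within-trial outcomes, such as cost per absolute working hour, do not use the QALY. The long-term decision tree and Markov model is driven by change in CVD risk score and takes inputs from the trial and the literature. Nothing shows that its QALYs use WPAI or Nordic data.

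**6. Can the ICER effect be sized?** If the EQ-5D-5L gave an incremental gain E and the other surveys added an amount x, the ICER would change by the factor E/(E + x). The documents give neither E nor x, nor the sign of x, and they do not state that the sources are added. No figure follows.

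**7. Is a valid QALY still available?** Yes. Table 1 has the EQ-5D-5L collected at baseline, 6, 12 and 18 months.

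**The case against.** The strongest reply is that the paragraph is loosely worded. On this view three surveys feed the economic evaluation, and the text mislabels all three as QALY sources. The four sections listed in step 3 support this, and it may well be what was intended. It does not remove the defect, because Tertiary outcomes still says something else, and it is the only place where the source of the QALY is defined.

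A reader might go further and infer that productivity and pain are in fact counted twice. The documents do not support that. They contain no combining rule, and Economic evaluation analyses each outcome separately; reporting productivity in its own analysis does not count it twice. Pain is not among the four effectiveness outcomes there, and musculoskeletal disease enters that section only as a treatment cost. Double counting is a risk if the sources are merged, not a feature of the plan.

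A reader might also infer that every ICER in the study is compromised, or that the cost per QALY is biased by some percentage. Neither follows, for the reasons in steps 5 and 6.

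Finally, it is fair to say that this concerns a tertiary outcome and that the data needed for a valid QALY will be collected. That stands, and it limits the severity.

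**Conclusion.** The point holds in this form: the article fixes two QALY sources that give no utility, states no mapping, and conflicts with its own treatment of the same instruments elsewhere. Followed as written, the within-trial cost per QALY would be invalid and not comparable with other evaluations. If the sources were combined, there would also be a risk of counting usual activities and pain twice.

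The conclusion rests on the definition of a QALY and on what the WPAI and the Nordic questionnaire measure; it needs no numerical assumption. No size can be put on the ICER effect. The primary outcome and the sample size do not depend on the QALY. Severity is moderate: wrong as stated, but confined to one part of the economic evaluation and recoverable from data already planned.

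**What to change.** In Tertiary outcomes:

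1. State that within-trial QALYs are computed from the EQ-5D-5L index only, using the assessments at baseline, 6, 12 and 18 months.
2. Delete the reference to three surveys as QALY sources, and the words that make work productivity and musculoskeletal health further sources.
3. State that WPAI and Nordic results are analysed as separate outcomes in their own units, so that the section agrees with the Abstract, Measurement timeline of outcomes, Data analyses and Economic evaluation.

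The choice of value set and the way QALYs are accumulated over the visits can stay in the full protocol or analysis plan; their absence from the article is not part of this point.

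The cost is a change of wording. No instrument, visit or sample size changes. It should be made before outcome data are analysed, so that the QALY definition is not chosen after the results are known.

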#### Measurement timeline of outcomes

The primary outcome will be measured at baseline, 6th month, 12th month and 18th month follow-up. The non-invasive cardiometabolic outcomes will be measured at baseline and every 6 months until the 18th month. The invasive cardiometabolic outcomes will only be measured at baseline, 6th month and the 12th month. The tertiary outcomes such as the EQ-5D-5L, musculoskeletal health, WPAI and self-report comorbidities will be measured together with the non-invasive cardiometabolic measures at baseline, 6th, 12th and the 18th month (Table 1). The economic impact will be evaluated at 6th month and the end of the trial follow-up period.

**Table 1 Tab1:** Overview of study outcomes and measurement instruments used (docx)

	Baseline	6 months	12 months	18 months
Objectively measured sitting, upright time and step count				
10-day ActiGraph	x	x	x	x
Self-reported demographics				
- Age	x			
- Gender	x			
- Nationality	x			
- Marital status	x			
- Education	x			
- Pre-existing diseases	x	x	x	x
- Smoking and alcohol consumption	x	x	x	x
Questionnaire:				
- Work Productivity and Activity Impairment questionnaire (WPAI)	x	x	x	x
- General Physical Activity Questionnaire (GPAQ)	x	x	x	x
- EuroQol-5 Dimension (EQ-5D-5L)	x	x	x	x
- Standardised Nordic Questionnaire	x	x	x	x
- Health utilisation	x	x	x	x
Health-related outcomes				
- Body weight	x	x	x	x
- Body height	x	x	x	x
- Neck, waist, and hip circumference	x	x	x	x
- Blood pressure	x	x	x	x
Biomarkers				
- Fasting plasma glucose, HbA1c	x	x	x	
- Fasting insulin	x	x	x	
- Lipid profile: triglyceride, total cholesterol, high density lipoprotein cholesterol (HDL-C), low density lipoprotein cholesterol (LDL-C)	x	x	x	
- High sensitivity C-reactive protein (hs-CRP)	x	x	x	

